### **3.6 Study Endpoints and Follow-Up**

The primary endpoint is a composite defined as the earliest of: (1)  $\geq 40\%$  decline in eGFR from baseline; (2) onset of kidney failure (initiation of maintenance dialysis or kidney transplantation); or (3) all-cause mortality. These criteria mirror standard endpoints in CKD trials. Follow-up begins at the date of the index blood draw and continues until occurrence of the composite event, death, loss to follow-up, or end of study (up to ~10 years). Participants will be censored at the time of death if it precedes kidney endpoints, loss to follow-up, or at 10 years of follow-up to ensure comparability across cohorts.

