## 2. Objectives

The primary and secondary objectives are to:

- Develop and validate a plasma APOL1 proteomic risk score (APRS) for prediction of a composite kidney outcome ( $\geq 40\%$  decline in eGFR, initiation of dialysis or kidney transplantation, or all-cause death) in APOL1 high-risk individuals with preserved kidney function.

- Compare APRS performance (discrimination) to standard models including the KFRE, APOL1 genotype status, and CKD polygenic risk scores.

- Externally validate APRS in independent, ancestry-matched cohorts (ARIC and UK Biobank) using harmonized outcomes.

- Assess biological plausibility by evaluating the association of APRS protein components with kidney tissue pathology (e.g., interstitial fibrosis).

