## **3 Cohorts, inclusion criteria, and analytic sets**

Primary derivation set (APOL1-HR, preserved eGFR):

Inclusion: APOL1 genotype = high-risk (two risk alleles: G1/G1, G2/G2, G1/G2), available plasma proteomics (SomaScan platform), baseline eGFR > 60 mL/min/1.73 m^2 measured at or 2 months before or 1 month after of sampling, available UACR (or imputed as specified).

Final sample size in derivation set:  $N = 851$ . Baseline descriptive statistics, event counts, and follow-up summaries are provided in manuscript. Key cohort summary (derivation APOL1-HR preserved-eGFR): mean age 49.2 years; female proportion 66.5%; mean eGFR 90.6 mL/min/1.73 m^2; median UACR 17.23 mg/g; composite event rate 17.98% ( $n = 153$ ); mean time to event 6.51 years; median follow-up 7.3 years.

Secondary analytic sets:

APOL1-HR with existing CKD at baseline: 262 participants included for comparison and benchmarking of APRS behavior in established disease.

APOL1-low-risk extension: an additional 995 participants to evaluate specificity and cross-genotype performance.

EUR comparison set (review-only):  $N = 514$  (used for method comparisons but not central to the APOL1-focused primary aims).

External validation cohorts

ARIC (Atherosclerosis Risk in Communities): African-ancestry subset with SomaScan proteomics (where available).

UK Biobank (UKB): African-ancestry subset with Olink proteomics (smaller targeted panels). Because platforms differ, apply the prespecified cross-platform mapping and multi-output imputation.

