### **6.3 Cox proportional hazards model**

#### **6.3.1 Censoring and the Assumption of Independence**

In survival data analysis, censoring occurs when an event is not observed due to termination of follow-up, loss to follow-up, or other reasons. To obtain unbiased estimates using Kaplan–Meier curves and Cox models, it is crucial that the censoring mechanism is independent of the actual event occurrence time. In this study, for outcomes other than death, patients censored due to loss to follow-up or the end of the 10-year follow-up period are assumed to be censored non-informatively.

Importantly, since all-cause mortality is included as an event within our composite outcome, deaths are treated as events rather than censoring. To address potential undercounting of events when using single-outcome definitions and to appropriately account for the competing risk of death, we construct a composite outcome that comprises  $\geq 40\%$  decline in eGFR, end-stage kidney disease, long-term dialysis, kidney transplantation, and all-cause mortality.

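### Protocol 3.6 censors participants at death although death is part of the primary composite; the SAP and the reported PMBB counts treat death as an event, so the clause must be corrected

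*Combined protocol and SAP*

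**What the plan says.** Protocol section 3.6 defines the primary endpoint as the earliest of a 40% or greater fall in eGFR, kidney failure, "or (3) all-cause mortality". The next statements in the same paragraph do not fit that definition. Follow-up "continues until occurrence of the composite event, death, loss to follow-up, or end of study (up to ~10 years"), which names death separately from the composite event. The paragraph then gives the censoring rule: "Participants will be censored at the time of death if it precedes kidney endpoints, loss to follow-up, or at 10 years of follow-up". Nothing there restricts the rule to a kidney-only or secondary analysis.

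Two other places take the opposite position. Protocol section 2 describes the outcome to be predicted as including "initiation of dialysis or kidney transplantation, or all-cause death) in APOL1 high-risk individuals with preserved kidney function". SAP section 6.3.1, the section devoted to censoring, says "since all-cause mortality is included as an event within our composite outcome, deaths are treated as events rather than censoring".

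**The concern.** The text contains two incompatible rules for the primary endpoint. Under one, a participant who dies without a kidney endpoint has an event at the date of death. Under the other, the same participant is censored on that date. The second rule turns the composite into a kidney-only endpoint and treats death as independent censoring, which SAP 6.3.1 says the composite was built to avoid.

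Nearly every main result depends on this event indicator: the penalised Cox coefficients, the time-dependent AUC, the number needed to treat (NNT) and the censoring weights. The code in SAP section 7 estimates the censoring distribution from the training data, so censored deaths would enter weights that protocol 3.7 intends for loss to follow-up. The protocol also promises harmonised outcomes across PMBB, ARIC and UK Biobank, and that requires one rule in all three.

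**Working it through.** **Inputs.** Counts for PMBB APOL1 high-risk participants with eGFR above 60 come from protocol Appendix 1 and SAP section 3; the training/test split from Supplementary Table 1; the group with eGFR at or below 60 from Appendix 2.

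**Reproducing the plan's figure.** 153 / 851 = 17.98%, as stated in SAP section 3 and Appendix 1. The split agrees: 121 + 32 = 153 composite events and 96 + 24 = 120 kidney events.

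**Events that exist only because death counts.** Composite events minus participants with a kidney event:

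| PMBB group | Composite | Kidney | Death only | Share of composite |
|---|---|---|---|---|
| High-risk, eGFR > 60 | 153 | 120 | 33 | 21.6% |
| – training | 121 | 96 | 25 | 20.7% |
| – test | 32 | 24 | 8 | 25.0% |
| High-risk, eGFR ≤ 60 | 145 | 125 | 20 | 13.8% |
| Low-risk, eGFR > 60, before matching | 142 | 90 | 52 | 36.6% |

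The deaths reconcile in the first row: 62 deaths, of which 120 + 62 − 153 = 29 also had a kidney event, leaving 62 − 29 = 33.

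**Which rule was used in PMBB.** If deaths before a kidney endpoint were censored, composite and kidney counts would be equal. In every row the composite is larger, so deaths were counted as events.

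**What the clause would change if followed.** The primary event count would fall from 153 (17.98%) to 120 (14.10%). Three illustrations:

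- *NNT.* With the 27% relative risk reduction in protocol 3.7 and crude whole-cohort rates, 1 / (0.1798 × 0.27) = 20.6, against 1 / (0.1410 × 0.27) = 26.3.
- *Power.* The Schoenfeld inputs of SAP 8.1 (p = 0.3, HR 1.648, two-sided 0.05) reproduce the stated figure: 85% power needs N = 685.3 at a 25% event rate. With D events, power = Φ(√(0.21 D) × ln 1.648 − 1.96). This gives 0.81 for D = 153 and 0.71 for D = 120, using all 851 participants.
- *Genotype comparison.* Appendix 1 already shows the sensitivity. High-risk against low-risk gives P = 0.09 for the composite and P < 0.01 for kidney events (0.16 and < 0.01 after matching).

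**Ten-year risk, approximate.** Time at risk ends at death under either rule; only the event indicator changes. Taking 851 × 6.51 = 5,540 person-years and a constant hazard:

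- deaths as events: 1 − exp(−10 × 153 / 5,540) = 24.1%
- deaths censored: 1 − exp(−10 × 120 / 5,540) = 19.5%

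**The case against.** The strongest reply is that the documents already settle the matter. Protocol section 2, the endpoint definition in 3.6 and the SAP's own censoring section all count death as an event, and the PMBB tables show that this was done. On that view the clause is a slip with no demonstrated effect on any result. The factual part stands: no loss of events occurred in PMBB.

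A second reply is that the clause speaks of death preceding kidney endpoints, and the tables carry a separate kidney-event row. Censoring at death would suit a cause-specific analysis of that outcome. This may be what was meant, but section 3.6 defines no kidney-only endpoint and attaches the clause directly to the primary composite. The missing restriction is itself the defect.

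A reader might infer more than the documents support in two ways:

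- *That about 22% of primary events were lost.* The tables contradict this.
- *That ARIC or UK Biobank analysts scored a different endpoint.* Protocol 3.4 lists mortality among the UK Biobank outcomes, section 2 calls for harmonised outcomes, and no event counts are given for either cohort. A discrepancy there can be neither shown nor excluded.

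**Conclusion.** The contradiction is real and needs correcting: as written, section 3.6 gives a rule that would produce the wrong primary endpoint. The clause is the outlier, because the rest of the plan and the PMBB data follow the SAP. If it were applied literally, 33 of 153 primary events (21.6%) would be lost, including a quarter of those in the test set. That figure is plain subtraction of reported counts and needs no modelling assumption.

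The comparison of about 24% with 19.5% at 10 years is softer. It assumes a constant hazard and reads 6.51 years as the mean time to event or censoring over all 851 participants. That reading is plausible, since mean follow-up is 7.18 years, but the documents do not define the quantity. The lower figure also treats death as independent censoring. It should be quoted only with those labels. The NNT and power figures describe what would follow from the clause, not what happened.

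**What to change.** Replace the censoring sentence in protocol 3.6 with:

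*Death from any cause before a kidney endpoint is a primary event; participants without an event are censored at the earliest of loss to follow-up, end of study, or 10 years.*

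End of study must stay in the list. Section 3.6 already names it, and with mean follow-up of 7.18 years a rule limited to loss to follow-up or 10 years would leave no instruction for participants still under observation when data collection ends.

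If a kidney-only analysis is wanted, define it separately, label it cause-specific, and confine censoring at death to it.

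Confirm that the ARIC and UK Biobank endpoint code uses the PMBB rule, and report composite, kidney and death counts for each cohort so that readers can check. The cost is one protocol sentence, a code check in two cohorts and a few added table rows. The PMBB counts already follow the corrected rule.

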### **3.7 Statistical Analysis**

The APOL1–high-risk cohort will be randomly divided into an 80% training set and 20% test set (stratified by outcome incidence). In the training set, candidate proteins will be selected via an elastic-net penalized Cox proportional hazards regression (age, sex, baseline eGFR, and log2(UACR) included as unpenalized covariates). Tuning parameters ( $\alpha$ ,  $\lambda$ ) will be chosen by 8-fold cross-validation. The final APRS model will include the nine selected proteins plus the four clinical covariates. Model discrimination will be quantified

by time-dependent AUC (tAUC) at prespecified time points and Harrell's C-index. Model performance will be compared to the KFRE (4-variable equation) and established CKD risk scores.

Proportional hazards assumptions for APRS and covariates will be tested using Schoenfeld residuals. Sensitivity analyses will address potential biases: we will apply inverse-probability-of-censoring weighting (IPCW) to account for informative loss-to-follow-up, computing weights within the training set. Feature stability will be assessed via bootstrap resampling. We will compute net benefit using decision-curve analysis (assuming equal weight for false positives and negatives). To gauge clinical utility, we will calculate the number needed to treat (NNT) to prevent one composite event under a hypothetical APOL1-targeted therapy: assuming a relative risk reduction of 27% (as reported for inaxaplin), NNT will be derived as the reciprocal of the absolute risk reduction. Comparisons of NNT between APRS-based risk stratification and standard models (KFRE) will be reported. All tests will be two-sided with  $\alpha=0.05$ .

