#### 3.3 ARIC Study (Validation Cohort)

The Atherosclerosis Risk in Communities (ARIC) Study is a prospective U.S. cohort of men and women (15,792 participants at baseline, 1987–1989). For validation, we will use African-American ARIC participants with APOL1 high-risk genotype. Specifically, 314 African-American APOL1 high-risk individuals who attended visit 2 (1990–1992) were included. An additional 2021 African-American individuals with APOL1 low-risk genotype and 8,602 European ancestry APOL1 low-risk participants were included as external reference. Genotyping (TaqMan assays) and SomaScan proteomics (5K proteins) were available on visit-2 samples. Follow-up (ascertainment of outcomes) is truncated at 10 years from

visit 2 to harmonize with the PMBB analysis. All ARIC analyses were approved under study application MP4524.

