#### **6.3.2 Proportional Hazards (PH) Assumption**

Due to our study population being relatively healthy and the lack of significant therapeutic interventions, the potential for treatment-induced time-dependent effects is minimized. However, even in this context, factors such as aging and dynamic changes in protein expression over time could still lead to violations of the PH assumption. To validate this assumption, we will use Schoenfeld residuals tests to assess the correlation between residuals and time. Graphical diagnostics, such as log-minus-log survival plots, will also be employed to verify that the hazard functions remain parallel across groups. If any covariate exhibits evidence of non-proportionality, we plan to introduce time-dependent covariates or apply stratified Cox models to adequately adjust for such effects.

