### 1. Data Preparation

Align predicted risk scores with true survival outcomes.

Apply inverse probability of censoring weights (IPCW) on the test set to adjust for censoring. The IPCW for sample  $i$  at time  $t$  is calculated as:  $IPCW_{i,t} = \frac{1}{\hat{S}(t|X_i)}$  where  $\hat{S}(t|X_i)$  is the estimated probability of being uncensored at time  $t$  given the covariates  $X_i$ .

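### Harrell's C is planned with no time horizon or censoring adjustment, so its values may not be directly comparable between PMBB, ARIC and UK Biobank (minor)

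*Combined protocol and SAP*

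**What the plan says.** Protocol section 3.7 plans two discrimination measures: "time-dependent AUC (tAUC) at prespecified time points and Harrell's C-index". It names no horizon for the C-index and no weighting. The same section adds a sensitivity analysis, "we will apply inverse-probability-of-censoring weighting (IPCW) to account for informative loss-to-follow-up", which is not tied to the C-index.

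SAP section 7, the detailed evaluation plan, never mentions a C-index. Its first step is to "Apply inverse probability of censoring weights (IPCW) on the test set to adjust for censoring". It then defines a time-dependent AUC and classification metrics from those weights.

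On follow-up, SAP section 3 reports a "composite event rate 17.98" per cent (153 of 851) in the PMBB derivation set, with "mean time to event 6.51 years; median follow-up 7.3 years". Appendix 1 gives follow-up of 7.18 years (SD 2.89). Protocol section 3.6 censors everyone "at 10 years of follow-up to ensure comparability across cohorts". Section 3.3 says of ARIC: "Follow-up (ascertainment of outcomes) is truncated at 10 years from" visit 2.

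SAP section 6.3.2 accepts that "factors such as aging and dynamic changes in protein expression over time could still lead to violations of the PH assumption". It plans Schoenfeld tests and log-minus-log plots, with time-dependent covariates or stratification if a violation is found.

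**The concern.** Harrell's C counts only pairs in which the earlier time is an observed event. Censoring removes late pairs more often than early ones, so a heavily censored cohort gives early events extra weight. If the score ranks early events better or worse than late ones, C moves with the censoring pattern although the score itself has not changed.

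PMBB is a health-record biobank and ARIC a research cohort with a fixed visit, so their censoring within 10 years may well differ. External validation is a stated objective. A reader will set the PMBB, ARIC and UK Biobank C values side by side, and part of any difference, or of any agreement, could come from follow-up rather than from performance.

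**Working it through.** **1. Censoring in PMBB.** The plan's event rate reproduces: 153/851 = 17.98%. So 698/851 = 82.0% have no observed event. Mean follow-up falls 10 − 7.18 = 2.82 years short of the horizon. If the median of 7.3 years is an ordinary median, at least 426 of 851 participants were followed for no longer than that. Even if all 153 events were among them, 426 − 153 = 273 (32%) were event-free and censored by about year 7.3.

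**2. What the two indices estimate.** Let T be observed time, δ the event indicator, η the score and G(t) the probability of remaining uncensored to t.

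- Harrell: C = Σ δᵢ·1(Tᵢ<Tⱼ)·1(ηᵢ>ηⱼ) / Σ δᵢ·1(Tᵢ<Tⱼ). If censoring does not depend on the score, a pair anchored by an event at t carries weight G(t)².
- Uno: the same sums, with each term divided by the estimated G(Tᵢ)² and restricted to Tᵢ<τ. The weight cancels, so the target depends on τ and not on G.

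Illustration, with censoring uniform on 2 to 14 years (an assumption): G(8) = 6/12 = 0.5. Pairs anchored at year 8 then count 0.25 as much as pairs anchored before year 2.

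**3. Size, matched to PMBB.** The documents give no C-index, no hazard shape, no censoring curve and no pattern of effect over time. These are assumed:

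- potential censoring uniform on 2 to 14 years, capped at 10, with mean (8/12)×6 + (4/12)×10 = 7.33 years;
- about 18% events and mean observed time about 6.5 years;
- log-risk SD 1.0 or 1.5;
- log-hazard effect constant, or 15% or 30% above its average before year 4 and as much below it afterwards, or the reverse. When weakening, the later effect is 0.85/1.15 = 74% or 0.70/1.30 = 54% of the earlier one.

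Harrell's C under this censoring, minus its value with everyone followed to 10 years, over repeated runs:

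| Effect of the score over time | Shift in Harrell's C |
|---|---|
| Constant (proportional hazards) | +0.004 to +0.009 |
| Weakens (15% or 30%) | +0.014 to +0.026 |
| Strengthens (15% or 30%) | −0.002 to −0.023 |

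Uno's C stayed within about 0.004 of the complete-follow-up value.

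**4. Wider grid.** Log-risk SD 0.8 to 1.6, Weibull shape 1.0 or 1.3, and three censoring shapes with mean 7.0 to 7.2 and SD 2.8 to 3.0 years. The shift was:

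- proportional hazards: +0.001 to +0.010;
- effect falling to 60% after year 3: +0.010 to +0.028;
- effect falling to 30%: +0.026 to +0.046, an extreme case.

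Uno's C was within about 0.006 throughout. Under proportional hazards with log-risk SD 1.2, Harrell's C was about 0.78 and the 10-year AUC about 0.81.

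**5. Scale against sampling error.** Hanley-McNeil at AUC 0.80: Q1 = 0.8/1.2 = 0.667 and Q2 = 2×0.64/1.8 = 0.711. For the test set (32 events, 139 without):

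SE = √[(0.16 + 31×0.0267 + 138×0.0711)/(32×139)] = √(10.8/4448) = 0.049.

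For all 851 (153 and 698) the same formula gives 0.022. Simulating Harrell's C directly at n = 171 gave an SD of 0.034 to 0.036.

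**The case against.** The strongest reply is that the plan already has a censoring-adjusted measure. Time-dependent AUC is listed first, SAP section 7 gives it inverse-probability-of-censoring weights, and the C-index is absent from that section. This largely stands, and it is why the point is minor. Two gaps keep it from closing the matter:

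- The prespecified time points are never listed, so no common horizon is fixed.
- The source of the weights is unsettled. The text of SAP section 7 conditions them on covariates and applies them to the test set, while its code fits one marginal censoring curve to the training data. Neither says which curve serves ARIC or UK Biobank.

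Other replies also stand. The shift is smaller than the test-set standard error. No test, threshold or model choice depends on Harrell's C. Comparing APRS with KFRE inside one cohort uses the same participants and the same censoring, so differences in follow-up between cohorts do not confound it. The plan also checks proportional hazards and has a remedy.

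A reader might go further and infer that PMBB discrimination is inflated by 0.02, or that C values cannot be compared because the other cohorts were followed longer. The documents support neither. SAP section 6.3.2 gives no direction for a departure from proportional hazards, and a strengthening effect reverses the sign. All cohorts are cut at 10 years, so only different censoring within that window remains.

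**Conclusion.** The point holds as a minor one. Harrell's C as planned has a target that moves with censoring, and PMBB is censored heavily enough for this to show. The shift is under 0.01 in the matched simulations if hazards are proportional (at most about 0.01 over the wider grid). It is about +0.015 to +0.025 if the score's effect weakens moderately, and down to about −0.02 if it strengthens. These figures rest on the assumed log-risk spread, censoring shape and time pattern; none can be read from the documents.

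The size of the PMBB-to-ARIC or PMBB-to-UK Biobank discrepancy cannot be determined, because the censoring distribution of those two cohorts is not reported. Nor should the result be read as Harrell's C overstating the 10-year AUC: under proportional hazards it lay below it. What can be said is that C values may not be directly comparable across cohorts, and that the planned weighted AUC covers this only in part.

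**What to change.** Add to protocol section 3.7 and SAP section 7:

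- Report Uno's censoring-weighted C-index for APRS and every comparator, truncated at one stated horizon that has adequate numbers at risk in every cohort (10 years at most).
- Estimate the censoring curve separately in each cohort, and state this for the time-dependent AUC as well.
- List the AUC time points and include the common horizon among them.
- Keep Harrell's C as descriptive, and base any reading across cohorts on Uno's C and the weighted AUC at the common horizon.
- Report the number at risk and the censoring pattern by year for PMBB, ARIC and UK Biobank.

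The core change is a sentence of SAP text and a standard function; the rest is reporting. The price is slightly wider intervals from the weights, and possibly a horizon shorter than 10 years if one cohort is thin late on. No new data are needed.

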## 1. Background

Chronic kidney disease (CKD) affects over 850 million people worldwide and over 800,000 in the U.S., imposing substantial morbidity, mortality, and health-care costs. Individuals of African ancestry suffer a disproportionately high ESKD burden, driven in part by APOL1 high-risk genotypes (two risk alleles, G1 and/or G2). An estimated 4–5 million Black Americans (and tens of millions globally) carry APOL1 high-risk genotypes, which confer ~5-fold higher risk of kidney failure. However, most APOL1–high-risk carriers remain healthy; only ~20% progress to kidney failure. Emerging APOL1-targeted therapies (e.g., inaxaplin) offer promise for prevention, but their utility depends on identifying those high-risk carriers likely to progress before CKD develops. Currently, clinical risk equations (such as the Kidney Failure Risk Equation [KFRE]) perform poorly when eGFR is preserved. Broad plasma proteomic profiling can capture subclinical renal injury and dynamic biology that genomic or creatinine-based measures may miss. In our preliminary analyses, multiple circulating protein biomarkers were associated with long-term kidney outcomes in APOL1–high-risk individuals. We now propose to refine and validate APOL1 Proteomic Risk Score (APRS) for early risk stratification in this population.

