## **2 Background and Rationale**

Chronic kidney disease remains a major global health burden, affecting an estimated 10–15% of the population worldwide. Individuals of African ancestry experience a disproportionately higher incidence of chronic kidney disease and progression to end-stage kidney disease. A key driver of this disparity is the presence of APOL1 high-risk alleles (G1 and G2). Individuals who carry two risk alleles (APOL1-HR genotype) face a significantly elevated risk of chronic kidney disease progression—yet most do not develop kidney disease, highlighting substantial phenotypic heterogeneity.

Although the APOL1 genotype is a well-established driver of kidney disease risk, not all carriers of HR alleles progress to end-stage kidney disease. Large-scale studies have estimated that ~20% of individuals with APOL1-HR may eventually develop kidney failure. Current clinical tools, including the Kidney Failure Risk Equation and other creatinine-based or albuminuria-based formulas, often underperform in predicting kidney outcomes at earlier stages (estimated glomerular filtration rate, eGFR  $\geq 60$  mL/min/1.73m^2). Consequently, there is an urgent need for noninvasive biomarkers that can distinguish individuals at greatest risk, enabling timely interventions (e.g., APOL1 inhibitors, stricter blood pressure control, etc.).

High-throughput proteomics (e.g., SomaScan®, Olink®) has become increasingly accessible for large patient cohorts. Circulating protein levels may reflect underlying pathophysiological mechanisms more directly than genetic risk alone. Our preliminary data in African American patients with APOL1-HR genotypes identified multiple protein signals that correlate with adverse renal outcomes. In this study, we comprehensively assess the utility of these protein markers in a combined protein-clinical model, test their incremental value beyond genetic or clinical risk factors, and validate the model in independent cohorts.

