### **6.4.3 Final modeling:**

After the iterative sampling and model fitting process, the best-performing model was identified based on the lowest cross-validated partial likelihood deviance within the testing set. The final set of selected proteins and their corresponding coefficients were then used to construct the prognostic model. This finalized model was refitted on the entire training dataset to derive the final coefficients, which were subsequently applied to generate the APOL1 Proteomic Risk Score (APRS) with the clinical confounders for downstream validation and external cohort analyses.

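### No planned analysis isolates what the nine proteins add to the four clinical covariates, although SAP section 2 says this will be tested

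*Combined protocol and SAP*

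**What the plan says.** Protocol 3.7 defines the score: "The final APRS model will include the nine selected proteins plus the four clinical covariates". The covariates are age, sex, baseline eGFR and log2(UACR), which in the selection step are "included as unpenalized covariates". SAP 6.4.3 adds: "This finalized model was refitted on the entire training dataset to derive the final coefficients". The outcome is the composite in Protocol 3.6: an eGFR fall of 40% or more, kidney failure treated by dialysis or transplant, or death from any cause.

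Comparators appear in two places. Protocol 3.7 says "Model performance will be compared to the KFRE (4-variable equation) and established CKD risk scores". The objectives in Protocol 2 say "Compare APRS performance (discrimination) to standard models including the KFRE, APOL1 genotype status, and CKD polygenic risk scores". The NNT comparison in Protocol 3.7 is also made against KFRE. Protocol 1 says that equations such as KFRE "perform poorly when eGFR is preserved", which describes the primary cohort.

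SAP 2 states a further intention, to "test their incremental value beyond genetic or clinical risk factors". SAP 6 and 7 give no clinical-covariates-only model, no nested likelihood-ratio test and no difference in C-index or AUC between two models. The evaluation in SAP 7 produces metrics for one score at a time.

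**The concern.** APRS has two sources of advantage over an existing equation. Its clinical terms are estimated for this composite in this population, and it contains proteins. A comparison with KFRE shows the sum of the two. If the clinical terms alone, fitted to this outcome, would already beat KFRE, the plan as written would credit that part of the gain to proteomics. The same holds for the NNT comparison.

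What is at stake is the claim that a proteomic assay improves on routine clinical variables. SAP 2 says that claim will be tested, and a reader deciding whether the assay is worth using needs the answer. The other named comparators do not supply it: neither polygenic scores, nor genotype status, nor the unspecified established CKD scores are described as the same four covariates fitted to the same outcome.

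**Working it through.** **1. Counts.** Inputs are from Supplementary Table 1; totals are training plus test.

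| | Training | Test | Total |
|---|---|---|---|
| Participants | 680 | 171 | 851 |
| Composite event | 121 | 32 | 153 |
| Kidney event | 96 | 24 | 120 |
| Deceased | 48 | 14 | 62 |
| End-stage kidney disease | 23 | 3 | 26 |
| Dialysis | 12 | 3 | 15 |
| Transplant | 7 | 3 | 10 |

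The SAP's own figure reproduces: 153/851 = 17.98%, as in SAP 3. The totals 153, 120 and 62 also match Appendix 1.

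**2. How far the composite departs from kidney failure.**
- Deaths without a kidney event: 153 − 120 = 33, and 33/153 = 21.6%. In the test set, 32 − 24 = 8, and 8/32 = 25%.
- Cross-check: 62 + 120 − 153 = 29 participants had both a kidney event and death, and 62 − 29 = 33.
- Participants with ESKD, dialysis or transplant: at most 26 + 15 + 10 = 51 if the categories never overlap, and at least 26 if they overlap fully. That is 26/153 = 17.0% to 51/153 = 33.3%. In the test set it is 3 to 9 of 32.

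So at least 153 − 51 = 102 of the 153 participants with a composite event have none of the three kidney-failure entries.

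**3. What the planned comparison estimates.** Let C4 be a Cox model with age, sex, eGFR and log2(UACR), fitted in the training set to the composite. For any discrimination measure,

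(APRS − KFRE) = (APRS − C4) + (C4 − KFRE).

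The first term on the right is the added value of the proteins. The second is the effect of fitting clinical covariates to this outcome and cohort. The plan yields only the left-hand side, because C4 is never fitted.

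**4. Can the second term be sized?** Not from the documents, which give no AUC for C4 or KFRE here. As an illustration only, suppose the proteins add nothing and cost nothing out of sample, so that APRS and C4 share an AUC of A. In a binormal model, a fixed score with correlation ρ to the clinical predictor has AUC = Φ(ρ·Φ⁻¹(A)). The apparent gain is A minus this value. Both A and ρ are assumed.

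| A | ρ = 0.5 | ρ = 0.7 | ρ = 0.9 |
|---|---|---|---|
| 0.65 | 0.074 | 0.044 | 0.014 |
| 0.70 | 0.097 | 0.057 | 0.018 |
| 0.75 | 0.118 | 0.068 | 0.022 |
| 0.80 | 0.137 | 0.078 | 0.024 |

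The range, 0.014 to 0.137, runs from negligible to substantial, so no single figure can be defended. Against C4 the gain in this scenario is zero in every row.

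**5. Precision in the test set.** The Hanley–McNeil variance is [A(1−A) + (n₁−1)(a−A²) + (n₀−1)(b−A²)]/(n₁n₀), with a = A/(2−A), b = 2A²/(1+A), n₁ = 32 events and n₀ = 171 − 32 = 139. Ignoring censoring, the standard error of a single AUC is 0.055 at A = 0.70 and 0.049 at A = 0.80. The precision of a paired difference also depends on the correlation between the two scores, which is unknown.

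**The case against.** Benchmarking against the equation in current use is a legitimate question, and it is the protocol's stated objective. Incremental value appears in the SAP background, not in the Protocol 2 objectives or the SAP primary aim. The objectives list is introduced as non-exhaustive, and the established CKD scores are unnamed, so a clinical-only model is not ruled out. This stands as a reason to keep KFRE and to add a model rather than replace the comparator. It does not close the gap: an intention with no specified method leaves the attribution to be settled after the data are seen.

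Three stronger readings are tempting, and the documents do not support them.

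- **That KFRE is used with its published coefficients.** The text says only that it is a four-variable equation and a standard model. No refit is described, but none is excluded.
- **That the genotype comparison is empty, with an AUC of 0.5.** High- versus low-risk status is indeed constant in the all-high-risk primary cohort. However, no section places the comparison there, and mixed-genotype sets are already in the plan: PMBB low-risk participants (995 in SAP 3), ARIC (314 high-risk and 2021 low-risk African-American participants) and UK Biobank (204 high-risk among 1,171 of African descent). The gap is that the set is not named.
- **That noise proteins would look just as good.** Selection is conditional on the clinical covariates, and Supplementary Table 2 gives eGFR-adjusted hazard ratios whose intervals exclude 1 for all nine proteins at eGFR ≥60 (for example WFDC2, 3.73, 2.89 to 4.81). These are single-protein estimates not adjusted for age, sex or UACR, so they do not measure what the score adds. They do make a pure-noise score an unrealistic description.

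**Conclusion.** The concern holds in this form: SAP 2 promises a test of added value beyond clinical risk factors, and no specified analysis delivers it. An APRS advantage over KFRE combines the effect of fitting four clinical covariates to this composite with the effect of the proteins. The outcome mismatch follows from the documents' counts: 21.6% of composite events are deaths without a kidney event, and at most one third of participants with an event had ESKD, dialysis or transplant. The size of the mix is not derivable, and the table in the working is illustration, not an estimate.

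The conclusion assumes that KFRE is not refitted to this composite, as its description suggests but does not state. Recalibration alone would leave discrimination unchanged; refitting its coefficients would narrow the gap. It does not follow that the proteins add nothing, or that the reported gain will be mostly clinical refitting.

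**What to change.** Add to Protocol 3.7 and SAP 7 a Cox model with age, sex, eGFR and log2(UACR), fitted in the same training set to the same composite and then frozen. Report the paired difference in C-index and tAUC (APRS minus clinical-only) with bootstrap confidence intervals in the test set, ARIC and UK Biobank. Base any statement about the proteins' added value on that difference. Keep KFRE and the polygenic scores as benchmarks, and state whether KFRE is used as published or refitted. Run the genotype-status comparison in the mixed-genotype sets already in the plan, and name them.

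The cost is one extra fit and one table row per cohort, with no new data. The reported gain may be smaller. With only 32 events the test-set difference will be imprecise. SAP 6.4.3, read literally, also uses the testing set to choose the model, which would favour APRS there, so the ARIC and UK Biobank differences matter most.
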